### Statistical considerations

#### Sample size and powering

Currently published data on alpha diversity change in patients undergoing HCT and/or IMT span different study types, vary in quality/granularity, and use different alpha diversity indices. The evidence available suggests larger decreases in alpha diversity at approximately 1-month post-HCT compared with baseline in patients who do not receive IMT relative to those that do.^2 6 8 18 19^ Fitting a mixed-effects model (with fixed effects for arm, time (day), their corresponding interaction and a random per-patient intercept effect) with quadratic splines at 5 df (3 internal knots) to longitudinal change in alpha diversity data (measured with inverse Simpson’s index) from baseline,^2^ IMT patients had an expected change in baseline alpha diversity at day 28 post-HCT 3.46 (pooled SE=2.19) units more than placebo (IMT mean change=−4.70, SE=1.44, n=14; placebo mean change=−8.16, SE=1.66, n=11). We have used these results on IMT post-HCT to design our study of IMT pre-HCT versus placebo.

Our null hypothesis is there is no difference between the change in days 28±3 days alpha diversity (inverse Simpson’s) post-HCT from baseline in patients receiving pre-HCT IMT compared with patients receiving placebo capsules (ie, the difference in between-arm changes from baseline is zero). Using a two-sample t-test to compare IMT-arm change to placebo-arm change with two-sided alpha controlled at 20%,^20 21^ we need 46 patients randomised 1:1 between IMT and placebo (23 per arm) to have ≥80% power to detect a between-arm difference of 3.46 units (with pooled SD of 5.45 estimated at day 28 post-HCT from mixed-effects model). To account for dropouts at a rate of up to 8% across both arms, we will recruit 50 patients in total. Modelling and sample size calculations have been performed using R V.3.6.1.

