### Analysis of primary estimand

The primary outcome of between-arm difference in alpha diversity change from baseline at day 28 (±3 days) will be analysed using a mixed-effects model, with change in alpha diversity from baseline as an outcome, with treatment arm, time, treatment-by-time interactions and stratification variables used in randomisation included as fixed effects and also a per-patient intercept included as a random effect. The subsequent model estimate for the treatment-by-time interaction term at day 28 will be the effect of interest as per primary estimand.

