**Figure 2 F2:**
[figure not shown]
‘Prehabilitation’ of the gut microbiome in MAST. Dynamics of the gut microbiota conventionally through the peri-HCT period are shown in black (as defined previously^6^); the red line is our predicted higher starting point and nadir for patients receiving a pre-HCT IMT in the MAST trial. GvHD, graft-versus-host disease; HCT, haematopoietic cell transplantation; IMT, intestinal microbiota transplant; ITU, intensive treatment unit; MAST, Microbiota Transplant Prior to Allogeneic Stem Cell Transplant.

The use of IMT in the context of immunosuppressed patients requires certain considerations above and beyond those of, for instance, conventional use of IMT in treating recurrent CDI.^28^ The use of a capsulised preparation is clearly more acceptable to this patient cohort than conventional IMT slurry and may be safer avoiding potential aspiration of slurry. The donor screening protocol used donors is in full accordance with UK recommendations,^9^ while the risk of CMV transmission via IMT appears extremely low,^29^ CMV negative donors are being used out of an abundance of caution. The window for IMT administration aims to be long enough after prior chemotherapy to allow full cell count recovery, but early enough before HCT to permit sufficient microbiota engraftment. This is important since the degree of microbiota engraftment has been associated with level of clinical improvement after IMT.^30^ Our experience to date is that IMT mitigates the risk of invasive infections related to MDROs rather than decolonises them from the gut,^15^ but there is still uncertainty regarding this; one recent trial of IMT in a renal transplant population suggested certain extended-spectrum beta-lactamases (ESBL)-colonising strains being displaced by non-ESBL strains by strain competition.^31^ The serial clinical assessment and collection of shotgun metagenomic data from study participants in a placebo-controlled fashion will allow a much more granular assessment of the impact of IMT on MDROs than has been described previously.

In conclusion, the MAST trial aspires to give new clinical and translational insights into the role of gut microbiome manipulation in patients with haematological malignancy receiving allogeneic HCT, with particular focus on the potential role of IMT on haematological and infective outcomes. The study aims to run recruitment for 24 months postauthorisation and close in May 2027.

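### With only a per-patient random intercept named, the primary model's day-28 standard error rests on the average variance over visits, so the planned 20% error rate holds only if visit variances are equal

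*Protocol article*

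**What the plan says.** Under Analysis of primary estimand, the outcome is change in inverse Simpson's index from baseline. Arm, time, their interaction and the stratification variables are "included as fixed effects and also a per-patient intercept included as a random effect". The target is one time point: "The subsequent model estimate for the treatment-by-time interaction term at day 28 will be the effect of interest as per primary estimand".

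Under Sample size and powering, the design is a two-sample t-test "with two-sided alpha controlled at 20" per cent. It states that "we need 46 patients randomised 1:1 between IMT and placebo (23 per arm) to have ≥80% power" for a "between-arm difference of 3.46 units (with pooled SD of 5.45 estimated at day 28 post-HCT from mixed-effects model"). The planning model has the same form: fixed effects for arm, time and their interaction "and a random per-patient intercept effect".

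The primary estimand adds that other response-assessment data stay in the model when day 28 is unavailable. Analysis of secondary estimands refers to response assessments 1–5 and, separately, follow-up assessments 1–3. The provision for failed model assumptions stands under Analysis of secondary outcome measures, not under the primary analysis. Full methods are left to the SAP, which is not shown.

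**The concern.** A random intercept with independent, equal-variance residuals implies compound symmetry: one variance at every visit and one correlation between every pair of visits. The sample-size t-test uses only the spread at day 28. The analysis model replaces that spread with an average over all modelled visits. If day 28 is more variable than the other visits, the standard error is too small, the test rejects too often and the confidence interval is too narrow. If it is less variable, the test is conservative and power is lost.

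Either way the plan would no longer deliver the error rate it says it controls, on its only primary comparison. Equal variance cannot be taken for granted in a change score followed through conditioning and transplant. The Figure 2 legend anticipates marked movement over this period ("the red line is our predicted higher starting point and nadir for patients receiving a pre-HCT IMT in the MAST trial"), although it says nothing about variances.

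**Working it through.** **The plan's own figures.** Inputs from Sample size and powering: difference 3.46, SD 5.45, two-sided alpha 0.20, 23 per arm.

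- Standard error of the difference: 5.45 × √(2/23) = 1.61.
- Non-central t power: 80.3% at 23 per arm, 78.9% at 22. The stated 46 reproduces, and 46/0.92 = 50.
- The article reports "IMT mean change=−4.70, SE=1.44, n=14; placebo mean change=−8.16, SE=1.66, n=11". These give arm SDs of 1.44 × √14 = 5.39 and 1.66 × √11 = 5.51, pooled 5.44, which agrees with 5.45 to rounding.

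The 5.45 itself comes from a model described with a random intercept only, so it is not clear evidence of the spread at day 28 as distinct from other visits.

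**Formula.** Take complete data, n per arm, K visits, a separate mean for each arm and visit, and a random intercept with equal-variance residuals. Then:

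- model-based variance of the day-28 arm difference = (2/n) × average visit variance;
- true variance = (2/n) × day-28 variance.

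Let every other visit have SD equal to r times the day-28 SD, and let A = [(K − 1)r² + 1]/K. The model SE is 1.61 × √A, and the true type I error is 2[1 − Φ(1.2816 × √A)].

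**Assumptions.** The ratio r is assumed, because the article gives no SD at any visit other than day 28. K = 5 is taken from response assessments 1–5. The effect of interest is read as the arm difference at day 28 with visit categorical, which the article does not spell out.

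**Results, K = 5, n = 23 per arm.**

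| r | A | Model SE (true 1.61) | Type I error | 80% CI coverage | Power at 3.46 |
|---|---|---|---|---|---|
| 0.8 | 0.712 | 1.36 | 28% | 72% | 86% |
| 1.0 | 1.000 | 1.61 | 20% | 80% | 81% |
| 1.2 | 1.352 | 1.87 | 14% | 86% | 75% |
| 1.5 | 2.000 | 2.27 | 7% | 93% | 63% |

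Worked line for r = 0.8: A = (4 × 0.64 + 1)/5 = 0.712, √A = 0.844, 1.2816 × 0.844 = 1.081, and 2[1 − Φ(1.081)] = 0.28. The higher power on that line is only the counterpart of the excess type I error. Power here uses the normal approximation, hence 81% rather than 80.3% at r = 1.

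With K = 4 the range for r = 0.8 to 1.2 is 27% to 14%, so the number of visits matters little. If only two of five visits differ, at 0.8 times the day-28 SD, the type I error is 24%.

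**Simulation check.** REML random-intercept fits, 23 per arm, five visits, correlation 0.5, 300 runs per setting:

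- r = 0.75: mean model SE 1.31 against an empirical 1.60, 30% rejection under the null (formula 30%).
- r = 1: 1.61 against 1.57, 18% rejection.
- r = 1.5: 2.29 against 1.54, 6% rejection under the null and 64% power.
- Autoregressive correlation of 0.7 with equal variances: 1.61 against 1.55, 20% rejection.

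With complete data, then, unequal variance does the harm and the shape of the correlation does not.

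**The case against.** The strongest reply is that the article shows no unequal variances. It gives no visit-specific SDs, so the point is conditional. That stands, and it is why the result is given as a range in both directions.

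A reader might go further and infer a definite inflation: inverse Simpson's index cannot fall below 1, so values bunch at the nadir and spread out by day 28. The document does not support this. The modelled outcome is change from baseline. If raw values collapse towards the floor, the change is roughly a constant minus baseline, and its SD is about the baseline SD rather than small. With raw visit SD equal to k times the baseline SD and correlation ρ with baseline, SD(change) is proportional to √(1 + k² − 2ρk). For assumed k of 0.1 to 0.4 at the nadir and 0.5 to 1.0 at day 28, with four visits, the type I error is 17–25% at ρ = 0.5, 21–28% at ρ = 0.25 and 21–31% at ρ = 0. Values near 30% need no correlation with baseline together with full recovery of spread by day 28. Nor does the visible text state recovery by day 28; the planning means there are still −4.70 and −8.16.

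It is also fair to say that residual structure is ordinary SAP content, that a random intercept can sit beside visit-specific residual variances or robust standard errors, and that a parsimonious model suits about 46 patients. This limits the point without removing it: the article does state a covariance term, and its escape clause for failed assumptions is written for secondary outcomes.

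**Conclusion.** The point holds as a conditional weakness in the stated primary model. On the usual reading of a random-intercept model, the day-28 test has its planned 20% error rate only if the variance of change is the same at every modelled visit. Under assumed SD ratios of 0.8 to 1.2 the actual rate runs from about 28% to about 14%. The documents fix neither the ratio nor its direction.

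Two further inferences would be wrong. The sample size is not in error: it reproduces. With complete data the day-28 estimate is not biased; the fault lies in its standard error, test and interval. Only where day 28 is missing and other visits carry the information can the assumed variance and correlation also move the estimate. That effect was not quantified here. The unseen SAP may already allow unequal variances, which would settle the matter.

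**What to change.** State in the SAP that the primary model treats visit as categorical and uses a visit-specific (unstructured) covariance over the response assessments up to day 28, fitted by REML with Kenward-Roger degrees of freedom. Pre-specify the fallback if it does not converge: heterogeneous compound symmetry or heterogeneous Toeplitz, both of which keep a separate variance for day 28. Define the effect of interest as the arm difference in change at day 28. Confirm that the day 100, 200 and 365 follow-up visits do not enter the primary model; the estimand's reference to response-assessment data suggests this, but the model description does not say so.

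With complete data the standard error then returns to about 1.61 at the planned SD, whatever the spread at other visits. The cost is a few sentences and a standard software option. An unstructured matrix over five visits has 5 × 6/2 = 15 parameters against two for the random-intercept model, so the fallback may be needed at about 46 patients. The sample size need not change.

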##### Primary estimand

Population: Adults with ALL, AML, AL of ambiguous lineage, high-risk MDS, CMML, and CML in blast phase, considered suitable/fit for allogeneic HCT.

Treatment: Capsulised IMT versus matched capsulised placebo.

Variable: Stool microbiota diversity post-HCT is defined as the change in alpha diversity (measured as inverse Simpson’s index) between IMT administration(at 14±3 days prior to HCT) and 28±3 days after HCT.

Population-level summary: The model-produced estimate for the treatment×time interaction effect at day 28.

Intercurrent events: Death, adverse/serious adverse events (AEs/SAEs), rescue therapy outside of antibiotic use, loss to follow-up/withdrawal.

Strategy to handle intercurrent events: Treatment policy will be used to handle patient all defined intercurrent events, any patient response-assessment data collected postrandomisation will still be used in the analysis model if day 28 data is unavailable.

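### The primary effect is named as the day-28 treatment-by-time interaction in a change-from-baseline model, which in general is not the day-28 between-arm difference that the trial is powered on

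*Protocol article*

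**What the plan says.** Analysis of primary estimand specifies a mixed-effects model. The outcome is change in alpha diversity from baseline. The fixed effects are arm, time, arm-by-time and the stratification variables, and there is a random intercept per patient. The section then says: "The subsequent model estimate for the treatment-by-time interaction term at day 28 will be the effect of interest". The Primary estimand section gives the population-level summary in the same terms: "The model-produced estimate for the treatment×time interaction effect at day 28".

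Sample size and powering describes a different quantity. Under its null hypothesis, "the difference in between-arm changes from baseline is zero". The power calculation is described as "Using a two-sample t-test to compare IMT-arm change to placebo-arm change", and its target is "to detect a between-arm difference of 3.46 units (with pooled SD of 5.45 estimated at day 28 post-HCT from mixed-effects model". The 3.46 comes from two arm means at day 28: "IMT mean change=−4.70, SE=1.44, n=14; placebo mean change=−8.16, SE=1.66, n=11". Design and objectives, Outcomes, and the opening sentence of Analysis of primary estimand also name the between-arm difference in day-28 change as the primary outcome.

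The article does not state how time is coded, which visit is the reference, or whether baseline rows enter the model.

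**The concern.** If the outcome were raw diversity and baseline were the reference time, the day-28 interaction would be the between-arm difference in change, which is what is wanted. Here baseline has already been subtracted from the outcome. The between-arm difference at day 28 is then the treatment main effect plus the interaction. Taking the interaction alone subtracts a second reference.

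Any benefit already present at the reference visit goes into the main effect and drops out of the named primary effect. This matters for this trial because the treatment is given before conditioning so that diversity is raised early and then held. The Figure 2 caption predicts that treated patients will start higher and have a higher low point. That pattern puts part of the benefit in the main effect. A programmer who reports the named coefficient could then understate or miss a real day-28 benefit on the primary endpoint.

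**Working it through.** **Inputs from Sample size and powering.** Difference 3.46, SD 5.45, 23 per arm, "two-sided alpha controlled at 20" per cent, power at least 80%, dropout up to 8%.

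**Assumed, because the article does not give them.** Within-patient correlation ρ of change scores from 0.3 to 0.7; the same SD at the reference visit as at day 28; complete data; and the share of the day-28 difference already present at the reference visit, from none to all.

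**Step 1: reproduce the stated sample size.**
- Effect: −4.70 − (−8.16) = 3.46, a full difference between two day-28 arm means.
- n per arm = 2 × (1.2816 + 0.8416)² × 5.45² / 3.46² = 22.4, rounded up to 23.
- SE of the difference = 5.45 × √(2/23) = 1.61. Power is 80.8% by normal approximation and 80.3% by the exact noncentral t (22 per arm gives 78.9%).
- 46 / 0.92 = 50.

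So 46 evaluable and 50 recruited are correct for the day-28 between-arm difference.

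**Step 2: what the interaction measures.** Let D(t) be the between-arm difference in mean change at time t.
- Categorical time, post-baseline reference visit r: main effect = D(r); day-28 interaction = D(28) − D(r); the sum of the two is D(28).
- Linear time: D(t) = main effect + interaction × t, so the interaction is a slope difference per day.
- Zero-change baseline rows as the reference level: D(0) = 0, so the day-28 interaction = D(28).

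A simulated check (2,000 per arm, ρ = 0.5, a constant 3.46 at days 7, 14 and 28) agrees. With post-baseline visits only, the main effect was 3.42 and the day-28 interaction 0.03. With baseline rows added as reference, the main effect was 0 and the day-28 interaction 3.46.

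**Step 3: power of the interaction with a post-baseline reference visit.** Under a random-intercept model the per-patient SD is 5.45 × √(2(1 − ρ)), which is 6.45, 5.45 and 4.22 for ρ = 0.3, 0.5 and 0.7. Multiplying by √(2/23) gives SEs of 1.90, 1.61 and 1.24. Two-sided power at 23 per arm (normal approximation):

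| Share of 3.46 present at reference visit | Expected interaction | ρ = 0.3 | ρ = 0.5 | ρ = 0.7 |
|---|---|---|---|---|
| None | 3.46 | 71% | 81% | 93% |
| Half | 1.73 | 37% | 43% | 55% |
| All | 0 | 20% | 20% | 20% |

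The last row is simply the two-sided alpha and does not depend on ρ. In the middle row, 80% power would need 126, 90 or 54 per arm. The intended contrast has about 80% power at 23 per arm in every row.

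**The case against.** The strongest reply is that the authors probably mean the right thing and have named it loosely. The target is stated correctly in several places. For the sample size, they fitted the same kind of model with spline time and took the difference of two day-28 arm means from it, not a coefficient. Analysis of secondary estimands promises treatment effects with 80% CIs at response assessments 1–5 and follow-up assessments 1–3. If the first of those visits were the reference level, it would have no interaction coefficient of its own, so visit-specific contrasts or a baseline reference fit that promise better. Reference coding is also ordinary SAP content.

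This stands as evidence of intent. It does not correct the two sections that define the primary effect, and those sections are in the article, not left to the SAP. The baseline-row coding that would rescue the wording is not stated, and rows with no variance fit a random-intercept model poorly.

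Two stronger readings are tempting and are not supported. A reader might infer that a real benefit will be reported as null or as harm. At ρ = 0.5, a benefit of 5.0 at the reference visit falling to 3.46 at day 28 would give an expected interaction of −1.54 (SE 1.61), significant in the wrong direction about 37% of the time and in the right direction about 1%. But the 5.0 is an assumption. The documents give no early effect size, and the caption gives only a direction. A reader might also infer that the same replacement wording belongs throughout Secondary estimands. The quality-of-life variable there is scores, not change. If raw scores are modelled with baseline as reference, the interaction is already the difference in change, and adding the main effect would be wrong. The diversity estimand names days other than 28.

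**Conclusion.** The point holds as a mismatch between the named primary effect and the quantity that the trial tests and is sized for. The sample size itself is right.

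The discrepancy vanishes if zero-change baseline rows are the reference time. With a post-baseline reference visit, the effect on power runs from little or none (71–93% if no benefit is present at that visit) through substantial (37–55% if half is present) to total (20%, the alpha level, if all is present), against about 80% for the intended contrast. These figures rest on 23 complete patients per arm, SD 5.45 at both visits, a random-intercept structure and the assumed correlations. The share of benefit present early is unknown, though the trial's own rationale makes none the less likely case.

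The documents do not show that the authors intend to report the bare coefficient. They show that the plan names it, and this is worth correcting before unblinding, so that no choice between two primary estimates arises later.

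**What to change.** In Primary estimand and Analysis of primary estimand, define the summary as the model-based between-arm difference in mean change from baseline at day 28, that is, the treatment main effect plus the interaction evaluated at day 28, with its CI. This works however time is modelled. Categorical visits are one option, not a requirement.

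In Secondary estimands:
- For the alpha-diversity change outcomes, use the same visit-specific contrast at their own named days (7, 14, 100, 200 and 365).
- For quality of life, state whether raw scores or changes are modelled, and define the effect as the between-arm difference in change at each named visit. If raw scores are modelled with baseline as reference, the interaction already gives this.

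The cost is a few sentences in the protocol, matched in the SAP, and one contrast statement in the analysis program. The fitted model, the 46 evaluable patients and the 50 to be recruited stay as they are.

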### Analysis of secondary estimands

The complete-case analysis will follow the same model as defined in analysis of primary estimand (using only patients attending all visits as per estimand). Mixed-effect models incorporating a per-patient random effect alongside effects for time of assessment, and an interaction term of time-by-arm assessing changes in alpha diversity(inverse Simpson’s index, Chao-1, Shannon index, Faith’s PD) and β-diversity will provide treatment effects and 80% CIs at response assessments 1–5 and follow-up assessments 1–3 (see figure 1). Similar approaches will be used to assess changes in gut microbiome taxonomic composition based on shallow shotgun sequencing.

Overall survival (time from randomisation to death/date last seen alive) will be analysed using Kaplan-Meier methods and log-rank testing using the same stratification variables as per primary analysis model defined in analysis of primary estimand. Additional survival analysis will include non-relapse mortality and GvHD-free relapse-free survival.

